# 6 EARLY PATIENT WITHDRAWAL

## Treatment Withdrawal

During the course of the trial, a patient may withdraw early from treatment. This may happen for a number of reasons, including:

Unacceptable toxicity  
 AE/SAEs requiring discontinuation  
 Clinical decision  
 Patient decision

When the patient stops treatment early, the End of Study Form needs to be completed, along with any other relevant CRFs (e.g. a SAE Form). The reason for withdrawing early from treatment should be clearly documented in the medical records.

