## 6.1 Patient evaluability and replacement

### Dose escalation

The MTD will be based on DLTs observed within 6 weeks of completion of BKM120 treatment. DLTs will be assessed whilst the patient is on treatment and for up to 6 weeks after completion of treatment in all patients. Patients completing 14 days of BKM120 treatment who either complete the follow up period or withdraw early ~~from~~ experiencing DLT will be evaluable for dose escalation decisions. Patients who withdraw early for reasons other than experiencing DLT (e.g. progression) will be considered non-evaluable for dose escalation and replaced as necessary to complete each cohort. Patients replaced for dose escalation earlier than the 14 days will be followed up and considered evaluable for toxicity analysis.

### Expansion cohort and cohort 4

Secondary endpoints of changes in F-Misonidazole and in blood flow will be based on F-Miso PET-CT and perfusion CT scans prior to commencing BKM120 treatment and on the day that radiotherapy treatment commences. Patients who have data available from both scans will be considered evaluable for secondary endpoints. Patients withdrawn early or without scans will be considered non-evaluable for secondary endpoints and replaced as necessary to

complete each cohort. All patients who receive at least one dose of BKM120 will be followed up and will be considered evaluable for toxicity analysis.

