### 8.1 Dosing schedules: dose levels and BKM120 dose escalation plan

In this study, DLT is defined as the presence of the following:

1. Any  $\geq$  grade 3 non-haematological toxicity (excluding nausea, vomiting or diarrhoea) that requires hospital admission or which does not resolve to  $\leq$  grade 2 within 7 consecutive days of optimal treatment.
2. Any  $\geq$  grade 3 nausea, vomiting or diarrhoea will be considered DLT only if any of them persist for >48 hours despite maximum supportive care.
3.  $\geq$  Grade 3 pneumonitis
4. Any  $\geq$  grade 4 haematological toxicity.
5. Mood deterioration from baseline DLT will be any grade  $\geq 3$  mood change if BL score of 2. DLT will be any grade  $\geq 2$  mood change if BL score of  $\leq 1$ .

DLT will be considered to occur if the toxicity is attributed either to BKM120 or to its interaction with radiotherapy. Cohort 4 will only be opened if there is inadequate evidence that BKM120 alters tumour hypoxia or perfusion (see Section 12.1)

| DL                      | RT                                     | BKM120                      | BKM120 dose escalation plan                                                                                                                                                                                                                                                                                         |
|-------------------------|----------------------------------------|-----------------------------|---------------------------------------------------------------------------------------------------------------------------------------------------------------------------------------------------------------------------------------------------------------------------------------------------------------------|
| 1                       | 20Gy in 5 fractions
(days 8 - 14)   | 50 mg od
(days 1 to 14)  | Three patients will be entered
If 0/3 have DLT proceed to DL2
If 1/3 have DLT expand dose level to a total of 6 patients.
If none of the additional 3 patients develop DLT, proceed to DL2.
If any further patient(s) develop DLT ( $\geq 2/6$ ) the MTD is exceeded and the trial will be terminated.  |

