| 2                       | 20Gy in 5 fractions
(days 8 - 14)   | 80 mg od
(days 1 to 14)  | Three patients will be entered
If 0/3 have DLT proceed to DL3.
If 1/3 have DLT expand dose level to a total of 6 patients.
If none of the additional 3 patients develop DLT, proceed to DL3.
If any further patient(s) develop DLT ( $\geq 2/6$ ) the MTD will be defined as 50mg od.                   |
| 3                       | 20Gy in 5 fractions
(days 8 - 14)   | 100 mg od
(days 1 to 14) | Three patients will be entered
If 0/3 have DLT then the MTD is 100 mg od.
If 1/3 have DLT expand dose level to a total of 6 patients.
If none of the additional 3 patients develop DLT, the RPTD is 100 mg bd.
If any further patient(s) develop DLT ( $\geq 2/6$ ) the MTD will be defined as 80mg od. |
| Expanded cohort at RPTD | 20Gy in 5 fractions
(days 8 - 14)   | MTD dose
(days 1 to 14)  | Once the MTD has been reached a further 6 patients will be treated at the MTD of BKM120 with palliative RT.                                                                                                                                                                                                         |
| 4                       | 20 Gy in 5 fractions
(days 22 – 28) | At MTD
(days 1 to 28)    | This cohort will only be used if there is no evidence of BKM120 induced changes in the tumour microenvironment on functional imaging in cohorts 1-3. A total of six patients will be entered into this cohort.                                                                                                      |

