#### 8.4 Dose modification

If a patient is unable to tolerate BKM120 due to side-effects, then BKM120 will be stopped. Scheduled visits and all assessments should continue to occur except the dosing of BKM120. The BKM120 dose will not be reduced. For replacement of non-evaluable patients see Section 6.1.

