#### Dose escalation phase

Between 2 and 18 evaluable patients will be recruited to the dose escalation phase. The aim of this Phase I study is to define the MTD of BKM120 when used in combination with palliative thoracic radiotherapy. The starting dose will be 50mg od. Unless DLT occurs this will be escalated to 80mg od and then 100mg od. There will be no further dose escalation beyond 100mg od. The study uses a standard 3+3 cohort design. Three patients will be entered at each dose level. At minimum, the criteria for dose escalation will be that if, by 6 weeks after the 3rd patient in each cohort has completed treatment there is no DLT, then the study will proceed to the next dose level. There will be a continuous evaluation of safety data, and dose escalation will be reviewed in response to any emerging safety information, with the Chief Investigator reserving the right to prolong the duration between cohorts as appropriate. The first cohort of patients will be given the starting dose of 50mg od, consideration will be given to stopping the recruitment early whether 2 or 3 DLTs are observed – consequently the minimum number of patients recruited is 2. If no DLT is observed, 3 patients will be entered at the next higher dose level. If 1 DLT is observed, an additional 3 patients will be entered at the same dose level. This process will be repeated until MTD is reached. This is the dose level at which no more than 1 of 6 evaluable patients or 0 of 3 evaluable patients experience a DLT. As a result, the maximum number of evaluable patients that could be recruited is 18 (6 evaluable patients by 3 dose levels)

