## 17.5 Analysis of safety

### Dose escalation phase

The variables that define the DLTs and safety variables will be summarized by descriptive statistics with patients grouped according to dose level received. Number (with percentages) of patient with and without DLT will also be presented according to dose level.

### Expansion cohort and cohort 4

Safety and toxicity variables will be summarized by descriptive statistics to investigate the safety and feasibility of expanded cohort patients at MTD dose and cohort 4 patients at MTD dose for 3 weeks of BKM120.

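### Cohort 4 runs a new 28-day BKM120 and radiotherapy schedule, but no DLT count holds entry or marks the schedule as not tolerable

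*Protocol*

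**What the plan says.** Protocol section 8.1 sets out the dose levels in a table. Levels 1 to 3 give BKM120 on days 1 to 14 with radiotherapy on days 8 to 14, and each has a consequence for two or more DLTs in six patients. At level 1 the consequence is that "the MTD is exceeded and the trial will be terminated". At levels 2 and 3 the MTD becomes the dose below. The expansion row has no DLT count, but it repeats the schedule that has already passed at the MTD.

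The cohort 4 row gives the MTD on days 1 to 28 with radiotherapy on days 22 to 28. It opens only if imaging shows no effect in cohorts 1 to 3. Its only number is the size: "A total of six patients will be entered into this cohort". Section 16.1 repeats the trigger and the six patients. The early-stopping wording there ("consideration will be given to stopping the recruitment early whether 2 or 3 DLTs are observed") stands under the dose escalation phase and concerns the first cohort.

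Section 17.5 plans a descriptive summary only. Its stated subject is "the safety and feasibility of expanded cohort patients at MTD dose and cohort 4 patients at MTD dose for 3 weeks of BKM120". No threshold is given.

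On data and replacement, section 6.1 says "DLTs will be assessed whilst the patient is on treatment and for up to 6 weeks after completion of treatment in all patients". For the expansion cohort and cohort 4 it adds: "Patients withdrawn early or without scans will be considered non-evaluable for secondary endpoints and replaced as necessary to" (the aim being a full cohort). Section 6 opens with "During the course of the trial, a patient may withdraw early from treatment" and lists unacceptable toxicity among the reasons. Section 8.4 keeps patients who stop the drug for side effects on their scheduled visits and assessments, then says "For replacement of non-evaluable patients see Section 6.1".

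**The concern.** Section 1.4 says that no other trial combines BKM120 with radiotherapy. The escalation phase and expansion cohort therefore supply the only combined-treatment experience, all of it on the 14-day schedule. Cohort 4 adds 14 days of drug before radiotherapy. Later toxicity is plausible on the protocol's own account. Section 8.3 places transaminase rises typically in the first 6 to 8 weeks of treatment. It also reports a grade 5 pneumonitis after one month at 100 mg, with concurrent progression and unclear causality.

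Followed literally, the cohort 4 row lets entry go on after a DLT count that would reject a dose at levels 1 to 3. Whether the longer schedule is tolerable would then be judged after the events have been seen, although section 17.5 makes safety and feasibility a stated question for this cohort.

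**Working it through.** **Plan's own totals.** Section 16.1 gives 18 to 30 patients. Escalation 6 to 18, expansion 6, cohort 4 six: 6 + 6 + 6 = 18 and 18 + 6 + 6 = 30. This reproduces, with cohort 4 counted as a fixed six.

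**How different the schedule is.** Section 1.2 gives an effective half-life of about 40 h. The fraction of steady state after n daily doses is 1 − 2^(−24n/40):
- 7 doses: 1 − 2^(−168/40) = 0.946.
- 21 doses: 1 − 2^(−504/40) = 0.9998.

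Implied accumulation is 1/(1 − 2^(−24/40)) = 2.9, which agrees with the stated 3-fold. Drug levels during radiotherapy are therefore almost the same on both schedules; the new element is the longer exposure beforehand.

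**What the 14-day data can show.** At the MTD there will be 3 + 6 = 9 to 6 + 6 = 12 evaluable patients. As illustrations, the exact two-sided 95% upper limit for the DLT rate is 0.34 with 0 of 9 and 0.38 with 1 of 12. Both refer to the 14-day schedule.

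**How often the limit would be met.** The documents give no DLT rate for 28 days, so rates p are assumed. P(two or more DLTs in 6) = 1 − (1−p)^6 − 6p(1−p)^5:
- p = 0.10: 0.114
- p = 0.20: 0.345
- p = 0.40: 0.767

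As written, none of these outcomes has a stated consequence.

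**Comparison with the 3+3 rule.** A dose passes levels 1 to 3 with 0/3, or with 1/3 followed by 0/3. P(reject) = 1 − [(1−p)^3 + 3p(1−p)^2(1−p)^3]. At p = 0.20 this is 1 − (0.512 + 0.384 × 0.512) = 0.29. Once a level has been expanded after 1/3, it is 1 − 0.512 = 0.49.

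**Patients spared by a hold.** The DLT window is 28 + 42 = 70 days. Assumptions for the simulation: six patients entered at fixed intervals, DLT onset uniform over 70 days, DLT patients not replaced, entry held for good at the second observed DLT. Mean number not entered:

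| DLT rate | one entry per week | per 2 weeks | per 4 weeks |
|---|---|---|---|
| 10% | 0.01 to 0.02 | 0.05 | 0.11 |
| 20% | 0.05 | 0.18 | 0.39 |
| 40% | 0.18 | 0.60 | about 1.2 |

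**Replacement wording.** Two readings are open for a patient who has a DLT before the day-22 scan:
- Under 8.4 assessments continue after the drug is stopped. A patient with both scans is evaluable under 6.1 and is not replaced.
- Under 6.1, early withdrawal or a missing scan makes a patient non-evaluable for imaging and replaceable. This paragraph has no exception for DLT, whereas the escalation paragraph replaces only withdrawals for other reasons. It sets no cap.

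**The case against.** The strongest reply is that cohort 4 is not unprotected. Section 8.7 promises review of emerging safety data throughout, the TMG and IEPTOC oversee the trial (18.1, 18.2), SAEs are reported within 24 hours (13.6), and there are urgent safety measures and halt powers (22.5, 22.6) and individual discontinuation rules (8.3, 8.4). The MTD definition also stands in the synopsis and section 3 without restriction to the escalation phase, so a standard for judging two in six is available. Longer single-agent dosing at 100 mg is not new, radiotherapy dose and overlap are unchanged, and drug levels are near steady state by day 8.

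All of this stands and lowers the priority. None of it attaches an action to a DLT count in cohort 4. The one scheduled TMG decision in 8.7 concerns dose escalation and comes six weeks after a cohort's last patient completes radiotherapy. Interim analyses take place only if the IEPTOC asks for them (17.3).

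A reader might infer that DLT withdrawals will be replaced without limit. The documents do not support that as the result: 8.4 keeps such patients on assessments, those with both scans are evaluable, and the plan states six patients for the cohort. Replacement of a DLT withdrawal is one reading of an unclear sentence.

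Nor does it belong only in the SAP: a rule that stops entry governs conduct, and section 8.1 already carries it for dose levels 1 to 3.

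**Conclusion.** The point holds with modest priority. Cohort 4 is the only new drug and radiotherapy schedule in the 8.1 table with no DLT count that holds entry or marks the schedule as not tolerable. The replacement wording in 6.1 is ambiguous.

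Applying two in six would flag 11, 34 or 77% of cohorts at true rates of 10, 20 or 40%. A reader might infer that many patients would be protected. The table above does not support that: the mean spared stays below 0.4 at rates up to 20% and reaches about 1.2 only at 40% with slow entry. The main gain is a criterion fixed before the events are seen.

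The DLT rates, onset pattern and entry rates are assumptions, since the protocol gives none for this schedule. The flow chart was not available and could not be checked.

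**What to change.** In the cohort 4 row of section 8.1, add two sentences:
- If two dosed cohort 4 patients have a DLT, further entry and replacement are held pending TMG/IEPTOC review.
- Two or more DLTs among the first six dosed patients (or among fewer, if entry stops earlier) means that the 28-day schedule at that dose is reported as exceeding the tolerable limit.

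In section 6.1, state that any dosed cohort 4 patient with a DLT counts for this boundary, whether or not both scans were done. No dose change is needed. The MTD need not be relabelled, since the synopsis already ties it to cohorts 1 to 3.

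The change is wording only, because DLTs are already assessed in all patients to six weeks after treatment. There are two costs. A hold may leave fewer than six scan pairs. The boundary would also reject a schedule with a true 20% DLT rate 34% of the time, somewhat above the 29% for the 3+3 rule at levels 1 to 3. Because the hold is pending review, the committees can still resume entry.

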## 8.2 Management of drug administration

BKM120 will be supplied as 10mg and 50mg hard gelatin capsules. BKM120 will be administered on a continuous daily dosing from the morning of day 1, until the morning of the final RT treatment. A flat scale of mg/day will be used and the dose will not be adjusted to body weight or surface area. The dose levels and total number of days of BKM120 treatment for cohorts 1-3 and for cohort 4 are given in section 8.1.

The potential CYP3A4 interaction associated with BKM120 means that patients must avoid consumption of Seville orange (and juice), grapefruit (and juice), and exotic citrus fruits from 7 days prior to the first dose of study drug and during the entire study period. Regular orange juice is allowed.

The following general guidelines should be followed for BKM120 administration:

- Patients should be instructed to take the dose of BKM120 once daily in the morning at approximately the same time each day
- BKM120 should be taken one hour following a light breakfast
- Patients should not eat for 2 hours after the administration of each BKM120 dose
- BKM120 should be taken with a glass of water. Patients should swallow the capsules as a whole and not chew them
- Patients taking medicinal products that may alter the pH of the upper GI tract should follow guidance in section 9.3

If vomiting occurs during the course of treatment, re-dosing is not permitted. Missed doses will not be made up. The next dose must be taken as scheduled.

#### Mood alteration

There is some pre-clinical evidence that modulation of the AKT/GSK3 signalling pathway by neurotransmitters is important for the regulation of behaviour. Preclinical studies conducted in rats to investigate the effect of BKM120 of different neurotransmitters have shown that repeated administration of BKM120 resulted in an enhanced decrease in glutamate, dopamine, serotonin, and epinephrine as well as in an enhanced increase in GABA and HIAA.

As of September 2012, approximately 4% of patients treated with BKM120 at 100mg od developed G3/4 mood alteration. In order to lower the risk of BKM120 induced mood alteration, patients with a past or current history of significant psychiatric disorders will be excluded from the study. Patients will also have to satisfactorily complete two different mood questionnaires (PHQ-9 and GAD-7) in order to be eligible for entry. Patient's mood will be carefully monitored throughout the study using these questionnaires at each visit.

The following grading system will be used for this study:

| PHQ-9                                                                                                                           |          |               | GAD-7 |          |               |
|---------------------------------------------------------------------------------------------------------------------------------|----------|---------------|-------|----------|---------------|
| Score                                                                                                                           | Severity | CTCAE grading | Score | Severity | CTCAE grading |
| 0-4                                                                                                                             | None     | Normal        | 0-4   | None     | Normal        |
| 5-9                                                                                                                             | Mild     | Grade 1       | 5-9   | Mild     | Grade 1       |
| 10-19                                                                                                                           | Moderate | Grade 2       | 10-14 | Moderate | Grade 2       |
| 20-27                                                                                                                           | Severe   | Grade 3       | ≥15   | Severe   | Grade 3       |
| * Note: The grading guidance above may be overruled at the discretion of the Chief Investigator following a psychiatric review. |          |               |       |          |               |

At Screening, a patient as judged by the investigator or a psychiatrist to be ineligible or who meets the cut-off score of ≥ 12 in the PHQ-9 or a cut-off of ≥ 15 in the GAD-7 mood scale, respectively, or selects a positive response of '1, 2, or 3' to question number 9 regarding potential for suicidal thoughts ideation in the PHQ-9 (independent of the total score of the PHQ-9) or who otherwise exhibit any suicidal ideation regardless of the question 9 scoring will be excluded from the study.

During the study, patients who develop mood alteration that constitutes a DLT, or who indicate a positive response by selecting '1, 2, or 3' to question number 9 on the PHQ-9 or who otherwise exhibit any suicidal ideation regardless of the question 9 scoring must see a psychiatrist for diagnosis and determination of most appropriate medical treatment. Patients will then be followed twice weekly by patient self-rating mood scale and will be seen weekly by the psychiatrist until the symptoms have resolved to  $\leq$  grade 1 or baseline.

### Cardiac

Cardiac safety studies, conducted *in vitro* and *in vivo*, indicate a minimal risk of an electrophysiological effect of BKM120. As of September 2012 adverse cardiac events following BKM120 treatment were rare. Nevertheless, cardiac monitoring will be undertaken with an ECG prior to commencing BKM120 and repeated during the trial. Concomitant use of any medications known to cause QT prolongation is prohibited (a list of such medications is provided in Appendix 3).

### Liver

Liver function test (LFT) alterations have been observed in patients taking BKM120. These have mostly involved temporary increases in transaminase enzymes (ALT and/or AST). Transaminase elevations typically occur during the first 6 to 8 weeks of treatment start. Only a few of the patients with LFT alterations had other simultaneous observations like bilirubin increase or clinical symptoms related to impaired hepatic function. A recent safety review across Novartis-sponsored trials has identified several potentially drug-induced liver toxicity (DILI) cases in the absence of cholestasis and other explanatory causes. This protocol has applied a conservative selection criteria to restrict the inclusion of patients with abnormal LFTs. Liver function will be monitored throughout the study and BKM120 discontinued if bilirubin  $> 2.0 \times$  ULN or AST/ALT  $> 3.0 \times$  ULN occurs and hepatology advice will be sought and appropriate follow-up assessments will be carried out to event resolution or stabilization (for patients with Gilbert Syndrome these dose modifications apply to changes in direct bilirubin only).

Follow-up assessments may include (as clinically indicated):

- Evaluate if associated with the appearance or worsening of clinical symptoms of hepatitis or hypersensitivity such as fatigue, nausea, vomiting, right upper quadrant pain or tenderness, fever, rash or eosinophilia, or other organ involvement.
- Obtain bilirubin, serum Alkaline Phosphatase (ALP), creatine phosphokinase (CPK), lactate dehydrogenase (LDH), and blood count with differential to assess eosinophilia.
- Perform liver imaging (ultrasound, MRI, or CT) to evaluate liver disease including metastasis or new lesions, obstruction/compression, etc.
- Perform viral hepatitis and other serology tests:
  - Hepatitis C (HCV) serology and viral RNA, Hepatitis B (HBV) serology and viral DNA, Hepatitis A (HAV) Immunoglobulin M (IgM) and HAV total
  - Hepatitis E (HEV) serology: IgM and IgG, viral RNA
  - Herpes Simplex Virus (HSV), Cytomegalovirus (CMV), Epstein-Barr viral (EBV) serology
- Verify and record the use of concomitant medications, acetaminophen, herbal remedies, and other over the counter medications, or putative hepatotoxins, on the concomitant medications report form.

- Liver biopsy as clinically indicated to assess pathological change and degree of potential liver injury
- LFTs should be followed-up weekly until resolve to  $\leq$  grade 1, baseline or stabilisation (no CTCAE grade change over 4 weeks) and outcome documented on the respective AE and lab chemistry pages.

This guidance has been updated since the completion of the escalation phase. During the escalation phase grade 3 bilirubinaemia or transaminitis events would result in the discontinuation of BKM120 and if the event lasted for longer than 7 days qualify as a DLT.

